### **9.7 Handling of dropouts or missing data**

Subjects who provide at least one efficacy variable data during the treatment period are included in the primary analysis. If a subject early terminates the study prior to the end of the treatment period, his/her last efficacy variable data will be collected for analysis.

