### 9.1 Definition of analysis sets

**Full Analysis Set (FAS):** FAS includes all randomized subjects who received at least one dose of the investigational drug. The data set is the main analysis set of demographic data, baseline indicators, medical history and curative effect.

**Per Protocol Set (PPS):** PPS is a subset of FAS, which includes subjects who met all inclusion criteria, did not meet exclusion criteria, had primary endpoint efficacy indicators and did not have other major protocol deviations. The data set is used for the supportive analysis of efficacy.

**Safety Set (SS):** SS includes all randomized subjects who received at least one dose of investigational drug and had at least one safety evaluation. This data set is used for statistical analysis of safety indicators.

**PK Concentration Set (PKCS):** PKCS includes all randomized subjects who received at least one dose of investigational drug and had at least one measured plasma concentration of the investigational drug available after medication.

**PK Parameter Set (PKPS):** PKPS includes all randomized subjects who received at least one dose of the investigational drug and had at least one valid PK parameter of the investigational drug during the study.

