## **9.4 Scheduled efficacy analysis**

hypothesis-testing:

|                        |                                                                                   |
|------------------------|-----------------------------------------------------------------------------------|
|                        | Percentage change in body weight from baseline to W30 (one-sided $\alpha=0.025$ ) |
| Null hypothesis        | $H_0: \mu_T - \mu_C \geq 0$                                                       |
| Alternative hypothesis | $H_1: \mu_T - \mu_C < 0$                                                          |

$\mu_T$  is the mean percentage change of body weight from baseline in the first to fifth dose groups after 30 weeks of GZR18 treatment ( $\mu_T$  includes  $\mu_{T1}$ ,  $\mu_{T2}$ ,  $\mu_{T3}$ ,  $\mu_{T4}$  and  $\mu_{T5}$ , which corresponds to GZR18 s.c. 12 mg once every two weeks, GZR18 s.c. 18 mg once every two weeks, GZR18 s.c. 24 mg once every two weeks, GZR18 s.c. 48 mg once every two weeks and GZR18 s.c. 24 mg once-weekly respectively),  $\mu_C$  is the mean percentage change of body weight from baseline in the first to fifth dose groups after 30 weeks of placebo treatment.  $\alpha$  is significance level (Type I error rate).

Based on FAS, conduct effectiveness analysis on efficacy indicators. PPS as a supportive analysis result.

Primary endpoint analysis: the percentage of body weight change (%) from baseline at week 30 will be taken as the primary endpoint, which will be analyzed based on the covariance model (ANCOVA), where, with baseline body weight as the covariate and group as the fixed effect, and the change from baseline is the dependent variable. The following indicators will be then calculated: the least-squares mean (LSMean) and its two-sided 95% CI of the percentage of the change from baseline in both groups, as well as the LSMean difference between the treatment and control groups and its two-sided 95% CI.

Secondary endpoint analysis: The continuity variables will be analyzed by the same method as the primary endpoint analysis. The number of cases reaching the target end point

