### **Sensitivity analysis**

Sensitivity analysis of main efficacy indicators. The Mixed Model Repeated Measures (MMRM) method will be used to incorporate all time points from baseline to week 30 into the Linear Mixed model (LMM) as a supporting analysis to compare the efficacy differences between the treatment group and the placebo group. Consistent with the primary endpoint analysis method, some specific populations are excluded for comparison of efficacy between groups.

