### **9.8 Determination of sample size**

Based on the study results of similar drugs and the non-clinical data of GZR18 and the existing clinical human pharmacodynamic data of GZR18, it is estimated that the difference of the percentage of body weight change from baseline at W30 between GZR 18 and placebo group is 11% (GZR18 weight loss of 13%, placebo group weight loss of 2%), the combined standard deviation is 10%, the degree of grasp is 0.8, one-side  $\alpha$  0.025, GZR18 group: placebo group: 4:1, then the calculated sample size is 40 subjects for GZR18 investigational drug and 10 subjects for placebo. Considering the 20% dropout rate, 52 subjects receive GZR18 investigational drug and 13 subjects receive placebo actually. There are five dose groups of GZR18, including the 12 mg/18 mg/24 mg once every two weeks' group and the 24 mg (18 mg) once-weekly group, with 52 subjects in each investigational drug group and 13 subjects in the placebo group; The subjects in the 48 mg once every two weeks' group may not titrate 48 mg due to intolerance to AE, so the number of subjects in the GZR18 group is increased to 78 (65 subjects for the GZR18 investigational drug and 13 people for the placebo group). The total sample size is 338 subjects.

The number of people to be enrolled will be determined based on the assessment of data from nonclinical studies of GZR18 and some data from the clinical trial of GZR18, as well as the number of Phase II clinical trials of similar drugs under development or already marketed, and information considered sufficient by the investigator and sponsor to achieve the trial objectives.

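### Section 9.7 in effect carries dropouts' last weights forward to week 30 in the primary ANCOVA, and limits that analysis to a population narrower than the FAS

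*Protocol*

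**What the plan says.** Section 9.4 of the protocol fixes the endpoint at one time point: "the percentage of body weight change (%) from baseline at week 30 will be taken as the primary endpoint". The model is an ANCOVA with baseline weight as covariate and group as fixed effect. Sections 9.1 and 9.4 base efficacy on the FAS, defined thus: "FAS includes all randomized subjects who received at least one dose of the investigational drug".

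Section 9.7 sets its own entry rule: "Subjects who provide at least one efficacy variable data during the treatment period are included in the primary analysis". For early terminators it adds: "prior to the end of the treatment period, his/her last efficacy variable data will be collected for analysis".

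The repeated-measures model over all visits to week 30 enters only "as a supporting analysis to compare the efficacy differences between the treatment group and the placebo group". The flowchart in section 1.2 schedules body weight at 15 post-baseline visits from W2 to W30, and at the early termination visit.

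**The concern.** An ANCOVA of week-30 change has no place for a week-8 weight unless that weight is treated as the week-30 weight. Three features of this trial make that substitution doubtful.

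- **Exposure.** By Table 6-1 the target dose is first given at W10 (group 1), W14 (group 2) or W18 (groups 3, 4 and 5). A subject who leaves early contributes a weight from sub-target dosing and short exposure.
- **After stopping.** The protocol makes off-drug weight at W33 a separate endpoint (section 3.2) and describes weight recovery in general terms (section 2.1). It gives no ground for assuming that weight freezes at the last value.
- **Amount.** Section 9.8 plans for 20% dropout.

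At stake is the primary estimate, and with it the responder proportions, because section 9.7 is not confined to one efficacy variable. The two definitions of who is analysed also conflict: a dosed subject with no efficacy value during treatment is in the FAS but outside the primary analysis of section 9.7.

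**Working it through.** **Inputs from section 9.8.** Effect: "placebo group is 11% (GZR18 weight loss of 13%, placebo group weight loss of 2" (per cent). Spread: "the combined standard deviation is 10" (per cent). Dropout d = 20%, power 0.8, one-sided alpha 0.025, allocation 4:1.

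**The plan's own figure.** Placebo n = (1 + 1/4) × [10 × (1.960 + 0.842)/11]² = 8.11, giving 9 + 36. The stated 10 + 40 is reproduced if 0.025 is taken as two-sided: 9.82, giving 10 + 40. At the stated one-sided level, 10 + 40 is therefore conservative. Dropout: 10/0.8 = 12.5, so 13, and 4 × 13 = 52. Total: 4 × 65 + 78 = 338. The point below does not depend on this.

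**Effect estimated under carry-forward.** Let f be the mean share of the week-30 change already reached at dropout. It is assumed equal in both arms, because the protocol gives no figure.

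- Carry-forward contrast = 11 × [(1 − d) + d × f].
- Target A, the effect had all stayed on treatment: 11.
- Target B, the effect regardless of stopping if dropouts end at placebo level: 11 × (1 − 0.2) = 8.8.

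| f (assumed) | Carry-forward | Against A (11) | Against B (8.8) |
|---|---|---|---|
| 0.25 | 11 × 0.85 = 9.35 | −1.65 | +0.55 |
| 0.50 | 11 × 0.90 = 9.90 | −1.10 | +1.10 |
| 0.75 | 11 × 0.95 = 10.45 | −0.55 | +1.65 |

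At f = 0.50, dropout of 10% gives 10.45 (B: 9.90) and dropout of 30% gives 9.35 (B: 7.70). Carry-forward is unbiased for the effect regardless of stopping only if weight stays at its last value.

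**Scale.** The standard error for 52 against 13 is 10 × √(1/52 + 1/13) = 3.10. The errors in the table are thus 0.55/3.10 = 0.18 to 1.65/3.10 = 0.53 of a standard error.

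**Test of the null.** In the least favourable row, 9.35/3.10 = 3.02. With the SD unchanged, normal-approximation power is about Φ(3.02 − 1.96) = 0.85, still above the planned 0.8.

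**Interval width.** A simulation used linear loss with random slopes, week-30 SD about 10, 20% dropout spread over the visits, and an unadjusted comparison of 52 with 13. The mean 95% width was 11.98 under carry-forward, 12.30 had every week-30 value been observed, and 13.87 in completers. Carry-forward is 1 − 11.98/12.30 = 2.6% narrower than complete data would give. Coverage of 11 was 94.3%.

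**The case against.** The protocol never names carry-forward, and the rule could be read as saying only that the last value is kept. That does not help: section 9.7 puts these subjects into the primary analysis, and section 9.4 gives that analysis no other way to use an early weight. An MMRM over all visits and a per-protocol analysis are also planned. They show sensitivity but leave the headline number unchanged. The population conflict mainly affects subjects who leave before any post-baseline weight, probably few.

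Several stronger readings are tempting, and the protocol does not support them.

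- **A larger bias.** A reader might judge early leavers against 13% and late leavers against placebo level. The drug-arm mean with linear loss is 0.8 × 13 + 0.2 × 13 × t/30. Leaving at W4 gives 10.75: 2.25 below 13, but only 0.05 below 10.8 (0.8 × 13 + 0.2 × 2). Leaving at W26 gives 12.65: 1.85 above 10.8, but only 0.35 below 13. Switching targets picks the larger error each time, and a single-arm mean is not the 11-point contrast. The W26 case also needs 13 × 26/30 − 2 = 9.3 points regained in four weeks; no regain rate is given.
- **A markedly narrow interval.** The narrowing is under 3% with 13 placebo subjects. If placebo were pooled to 65, simulated coverage falls to about 90% with full regain, but that is mostly bias against a smaller standard error.
- **A distorted dose ranking.** This is possible, since titration differs between some groups, but it is not shown: groups 1 to 3 share the same doses through W12.
- **Weight still falling at week 30.** This is an inference from the titration schedule, not a statement in the protocol.

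**Conclusion.** The point stands in limited form. Sections 9.7 and 9.4 together amount to carry-forward for each early terminator who has an efficacy value, and section 9.7 conflicts with the FAS in section 9.1. With 20% dropout in both arms and f between 0.25 and 0.75, the primary contrast falls 0.55 to 1.65 points short of the on-treatment effect, or exceeds by 0.55 to 1.65 points the effect that applies if dropouts end at placebo level. Both f and the off-drug course are assumptions. The direction depends on the target, so the target has to be stated before the estimate can be interpreted. Rejection of the null is probably not at risk. What needs correcting is a stated rule that sets the trial's main number, when a better analysis is already planned on weights already scheduled.

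**What to change.** Amend section 9.7 before unblinding:

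1. Analyse subjects as randomised in the FAS of section 9.1, and remove the separate entry condition.
2. State the target effect. The MMRM addresses the on-treatment effect, assuming that missingness depends only on observed data.
3. Make the planned MMRM primary: post-baseline visits as outcomes, baseline weight as covariate, and the contrast at W30.
4. Add a sensitivity analysis for the effect regardless of stopping: multiple imputation from the placebo group, ANCOVA on each data set, and Rubin's rules. This also brings in FAS subjects with no post-baseline weight, whom the MMRM cannot use. Imputing from off-drug subjects with a W30 weight is not a dependable alternative, because withdrawers are scheduled only for an early termination visit.
5. Keep carry-forward as a sensitivity analysis only.
6. Derive the 5/10/15/20% responder endpoints from imputed W30 weights instead of carried-forward ones.

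The cost is protocol and SAP wording, some programming, and a slightly wider interval. No new data are needed.

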### **9.8 Determination of sample size**

Based on the study results of similar drugs and the non-clinical data of GZR18 and the existing clinical human pharmacodynamic data of GZR18, it is estimated that the difference of the percentage of body weight change from baseline at W30 between GZR 18 and placebo group is 11% (GZR18 weight loss of 13%, placebo group weight loss of 2%), the combined standard deviation is 10%, the degree of grasp is 0.8, one-side  $\alpha$  0.025, GZR18 group: placebo group: 4:1, then the calculated sample size is 40 subjects for GZR18 investigational drug and 10 subjects for placebo. Considering the 20% dropout rate, 52 subjects receive GZR18 investigational drug and 13 subjects receive placebo actually. There are five dose groups of GZR18, including the 12 mg/18 mg/24 mg once every two weeks' group and the 24 mg (18 mg) once-weekly group, with 52 subjects in each investigational drug group and 13 subjects in the placebo group; The subjects in the 48 mg once every two weeks' group may not titrate 48 mg due to intolerance to AE, so the number of subjects in the GZR18 group is increased to 78 (65 subjects for the GZR18 investigational drug and 13 people for the placebo group). The total sample size is 338 subjects.

The number of people to be enrolled will be determined based on the assessment of data from nonclinical studies of GZR18 and some data from the clinical trial of GZR18, as well as the number of Phase II clinical trials of similar drugs under development or already marketed, and information considered sufficient by the investigator and sponsor to achieve the trial objectives.

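### The inputs in protocol section 9.8 call for 36+9 evaluable subjects, not 40+10 (about 86% power), and section 9.4 leaves open which placebo comparator and which error rate the power and the 0.025 refer to

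*Protocol*

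**What the plan says.** Protocol section 9.8, repeated in the synopsis (section 1.1, statistical analysis), gives the inputs: "GZR18 weight loss of 13%, placebo group weight loss of 2" per cent, so a difference of 11 points; "the combined standard deviation is 10" per cent; and "the degree of grasp is 0.8, one-side" alpha of 0.025. It then concludes: "GZR18 group: placebo group: 4:1, then the calculated sample size is 40 subjects for GZR18 investigational drug and 10 subjects for placebo". Next comes the dropout step: "Considering the 20% dropout rate, 52 subjects receive GZR18 investigational drug and 13 subjects receive placebo actually". The 48 mg group is raised to 65+13, and the total is 338.

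Section 9.4 states one null hypothesis at one-sided 0.025. The treatment mean stands for five dose-group means, each with its own index. The control mean carries no index and "is the mean percentage change of body weight from baseline in the first to fifth dose groups after 30 weeks of placebo treatment". The section does not say whether its one-sided 0.025, defined with the words "is significance level (Type I error rate"), is per comparison or across the five.

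**The concern.** A sample size described as calculated should come back out of its own inputs, and this one does not.

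The power should also belong to the comparison that will be made. Section 9.8 sizes one dose against the placebo subjects randomised within that dose group. Section 9.4 appears to compare each dose with placebo subjects from all five groups, and no power is given for that.

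Finally, one alpha is attached to one null that covers five means. A reader of a later report could take 0.025 as the chance of a false positive anywhere in the primary analysis. At stake is a correct description of the design, and settling the comparator and the meaning of alpha before unblinding.

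**Working it through.** **Inputs.** From section 9.8: difference 11, SD 10, one-sided alpha 0.025, power 0.80, allocation 4:1, dropout 20%. From section 9.4: five treatment means and one placebo mean. From Table 6-1: 52 active subjects in four groups, 65 in the 48 mg group, 13 placebo in each.

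**1. The plan's own figure.** For 4:1 allocation, placebo n = (1 + 1/4) × ((z_alpha + z_power) × SD / difference)².
- As stated: 1.25 × ((1.960 + 0.842) × 10/11)² = 8.11, rounded up to 9, so 36+9 = 45.
- Power by noncentral t: 32+8 gives 77.4% and 36+9 gives 82.3%. The t-test therefore also needs 36+9.
- At 40+10: standard error 10 × √(1/40 + 1/10) = 3.536 and 11/3.536 = 3.11. Power is 86.2% (t) or 87.5% (normal).
- With one-sided 0.0125 (0.025 entered as two-sided) the normal formula gives 9.82, rounded up to 10, hence 40+10. By t-test the same alpha gives only 78.5% at 40+10.

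**2. The steps that reproduce.** 10/0.8 = 12.5, rounded up to 13; 4 × 13 = 52; 4 × 65 + 78 = 338.

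**3. Power for the possible comparators** (t-test, one-sided 0.025, 20% dropout, so 52 becomes 41 and 65 becomes 52).

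| Comparison | Evaluable | Power |
|---|---|---|
| One dose v its own placebo, as sized in 9.8 | 40 v 10 | 86% |
| 48 mg v its own placebo | 52 v 10 | 88% |
| A 52-subject dose v the placebo of the four 4:1 groups | 41 v 41 | 99.8% |
| A 52-subject dose v placebo of all five groups | 41 v 52 | 99.9% |

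**4. Family-wise error of five unadjusted one-sided 0.025 tests**, enrolled numbers, no effect at any dose.
- All placebo pooled (65): the tests are correlated through the shared control, with correlation √[n_i/(n_i+65) × n_j/(n_j+65)], for example 52/117 = 0.44 between two groups of 52. The result is about 9.5% by multivariate normal and by simulation.
- Placebo shared within each of the two random tables of section 6.3.1 (four doses v 52, 48 mg v its own 13): the four tests together give about 7.8%, and 1 − (1 − 0.078) × 0.975 is about 10.1%.
- Five separate placebo groups: 1 − 0.975⁵ = 11.9%.

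**5. Cost of control under pooling.** The one-sided Dunnett critical value for five doses is about 2.5. Power at 41 v 52 is then about 99.6%.

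**The case against.** The discrepancy is conservative. 40+10 exceeds the 80% target, the later steps are correct, and the trial is not underpowered. That stands, and it makes this a correction of wording.

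A reader might infer that 0.025 is the wrong error rate. It is not: it is correct for each comparison, whichever placebo is used, and the protocol never calls it family-wise or overall. Unadjusted pairwise tests are defensible in a phase II trial meant partly to inform dose selection (section 4.2.1). A multiplicity procedure may also sit in the statistical analysis plan, so its absence from the protocol is not the criticism. What remains is that the protocol itself writes one null over five means and labels its alpha as the type I error rate without a qualifier.

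A reader might also take pooling as settled and conclude that section 9.8 describes a test that is never run. The protocol does not use the word. Section 9.4 also speaks of two groups, and randomisation and blinding operate within dose group (sections 6.3.1 and 6.3.2). If each dose is compared with its own placebo, the basis of 9.8 does match the test, at about 86% and not 80%, and the wording of the control mean in 9.4 needs correcting instead.

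Entering 0.025 as two-sided would explain 40+10, but only under the normal formula. The protocol names no method, so this is a possibility and no more.

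**Conclusion.** The point holds in limited form. The calculated 40+10 is not what the stated inputs require: 36+9 is, and 40+10 has about 86% power. This rests only on the protocol's own inputs and a two-sample comparison of means. The baseline covariate in the ANCOVA would raise power further, by an amount that cannot be computed because no correlation is given.

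On the most natural reading of 9.4, power per dose is about 99.9%, far from the stated basis. On the own-placebo reading it is about 86%. The stated 0.80 matches neither.

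The 0.025 stands as a per-comparison level. Read across five unadjusted tests, the error is about 9.5% to 11.9%, depending on how placebo is shared. The documents do not support saying that the trial is underpowered, that 0.025 is wrong, or that a family-wise level of 0.025 was claimed.

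**What to change.** - **Section 9.8 and the synopsis:** state that the inputs require 36+9 evaluable subjects and that the chosen 40+10 gives about 86% power.
- **Section 9.4:** name the placebo comparator (all five groups, the groups of the same random table, or the dose group's own), and give in 9.8 the power for that comparator.
- **Alpha:** say that 0.025 is per comparison and that the family-wise error is about 10% (9.5% pooled, 11.9% with separate placebo groups). If an overall one-sided 0.025 is wanted, specify Dunnett or a fixed testing sequence with each test at 0.025.

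Make these changes before unblinding. They need no change in enrolment. Dunnett costs almost no power if placebo is pooled. A fixed sequence may leave some doses without a formal claim if a dose earlier in the order fails.

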### **9.9 Statistical software**

Unless otherwise specified, SAS 9.4 version or above will be used for all statistical analyses.

## **10. Regulation, Ethics, and Study Regulatory Requirements**

---

## **10.1 Regulation**

This study is conducted in accordance with the protocol, the ethical principles of the Declaration of Helsinki, ICH GCP harmonised guidelines, SOPs for Gan & Lee or its CRO, and other relevant regulations. The investigator and staffs of research centers must adhere to these principles.

In accordance with national and international regulations, this study may only be initiated after the required regulatory documents have been reviewed and approved by the Institutional Review Board (IRB)/Independent Ethics Committee (IEC) and the Certificate Authority (CA). The same process is also required for the implementation of the revised changes.

## **10.2 Informed consent**

In accordance with local regulations, ICH-GCP requirements, and ethical principles derived from the principles of the Declaration of Helsinki, informed consent must be obtained and documented prior to the patient's participation in the study.

Each signature of the subject (or his/her legal representative) on the written ICF must be personally dated by the signer. The ICF and any other notices for subjects are kept by the investigator as part of the trial records. Each subject or his/her legal representative must be provided with a signed copy of the ICF and any other notices for patients.

Prior to obtaining informed consent, the investigator (or designee) should provide study information verbally and in writing to the subject or his/her legal representative in a language and at a level of complexity that is understandable to the subject or his/her legal representative. Adequate time must be given to the subject or his/her legal representative to consider participation in the study. Each subject or his/her legal representative have the opportunity to discuss the study and its alternatives with the investigator.

An ICF is personally signed and dated by the subject or his/her legal representative and the person responsible for the informed consent (the investigator or designee) prior to participation in the study. A trial partner providing a supplementary explanation should also sign (or stamp) and date the ICF. The subject or his/her legal representative should be provided with a signed and dated copy of the ICF.

In addition, the subject will sign an IRB/IEC-approved consent form, as applicable (based on subject age and local requirements). In the informed consent process, each subject must agree to have direct access to his/her medical record for study-related monitoring, audits, IRB/IEC review, and regulatory inspection.

---

If the ICF is amended during the study, the investigator (or the sponsor, as applicable) must comply with all relevant regulatory requirements for the revised ICF approved by the IRB/IEC and use the revised ICF.

When additional relevant information becomes available, a second informed consent procedure may be required. The procedure shall be performed as directed by the sponsor.

The processes of informed consent and re-consent should be properly documented in the source documents.

